### Treatment fidelity

Fidelity to the treatment protocol will be assessed in 20% of treatment sessions for each child according to the following schedule: (1) 30 min of each of the first 3 treatment sessions, (2) an additional 3.3 h of treatment sessions randomly selected from the remainder of the intervention phase. A member of the research team will review these sessions using a DTTC fidelity checklist to determine adherence to the experimental treatment protocol. If clinicians fall below 90% fidelity during a treatment session, additional fidelity sessions will be scheduled with individualized feedback provided by one of the PIs. Once the clinician has achieved 90% fidelity, the planned fidelity schedule will be resumed.

### Recording and equipment

Each clinical site will record audio and video for all assessment and treatment sessions using an iPad (9^th^ generation) with a cardioid directional externally mounted microphone (Samson Satellite iOS/USB Broadcast Microphone). The iPad will be mounted on a UBeesize 50″ Extendable Lightweight Aluminum tripod stand located between 18 inches and 2 feet from the child. In addition, each clinical site will use a Zoom H1n 2-channel Handy Recorder audio recorder to capture probe data collection and to serve as a back-up recording for eligibility assessments. These recordings will be collected at a 96 kHz sampling rate with 24-bit encoding and saved to a Samsung – PRO 32 GB microSDXC UHS-I Memory Card.

## Discussion

### Potential significance

When the proposed study is complete, we will have measured treatment effects and generalization of DTTC in 60 children randomly assigned to groups with the same cumulative dosage that differ in dose frequency (i.e., low dose = treatment 2x/week for 12 weeks vs. high dose = treatment 4x/week for 6 weeks). Based on the extant literature [8, 22], we posit that both groups will demonstrate comparable improvements following the full dose (24 h) of treatment, but that between-group differences will be detected at other measurement points. We predict a group-by-time interaction, wherein the high dose group will demonstrate a significant advantage after 6 weeks of treatment as they will have completed 24 treatment hours compared to the low dose group, which will have completed 12 h of DTTC at that point. We also anticipate a group-by-time interaction for maintenance effects in which the high dose group will evidence superior maintenance of treatment and generalization gains compared to the low dose frequency group at the 4-week and 12-week post treatment follow-up sessions. If these hypotheses are correct, this study will provide evidence that DTTC treatment provided at a higher dose frequency yields faster and continued gains even after treatment is discontinued. More efficient service delivery will help children to progress through treatment in fewer years to develop functional speech. This may help reduce the risk of social-emotional challenges including anxiety and depression (e.g., [58, 59]). It may also result in the provision of better early intervention services and reduce long-term academic and vocational disparities for people with CAS [60, 61]. Alternatively, if treatment effects are shown but group differences are not detected, this will suggest that treatment schedule can be determined based upon available resources and family/clinician preference.

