### Current study

The proposed study aims to address these limitations by conducting an RCT to compare the effects of high and low dose frequency treatment schedules for a large sample of children with CAS undergoing DTTC speech treatment. To assess differences in treatment outcomes when dose frequency is varied, speech production accuracy will be tracked using whole word accuracy. The primary outcome measure will be whole word accuracy quantified using a multi-factor whole word accuracy measure, the Multilevel word Accuracy Composite Scale (MACS; [27]), which systematically accounts for segmental and prosodic accuracy, word shape maintenance, and smoothness and fluency of movement transitions. Secondary outcome measures will include phoneme accuracy (Percent Phonemes Correct; [28]), speech intelligibility (Intelligibility in Context Scale; [29]), and functional communication (Functional Outcomes on Communication Under Six; [30]). This RCT is expected to yield easily interpretable evidence to better understand the effect of dose frequency on treatment outcomes. We hypothesize that similar treatment and generalization gains will be detected for both the high and low dose frequency groups when cumulative dosage is constant (i.e., after 24 sessions have been completed). However, we predict that the high dose frequency group will demonstrate superior outcomes following 6 weeks of treatment when the high dose frequency group has completed 24 sessions and the low dose frequency group has completed 12 sessions. Based on our previous research [21, 22] and the extant literature, we also predict that the high dose frequency group will demonstrate superior maintenance of treatment and generalization gains compared to the low dose frequency group. Thus, while both conditions are predicted to yield positive treatment gains, we hypothesize the high dose frequency group to display these gains in a shorter timeframe and with greater maintenance and generalization as compared to the low dose frequency group.

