### Targeted enrollment

We plan to enroll 60 children with CAS with potential to recruit an additional 6 children to account for a 10% rate attrition if needed. The power analysis for the treatment effect comparing the Lower Dose Frequency treatment group to the High Dose Frequency treatment group during the immediate-post testing period was done using a latent growth curve model [31, 32]. Specifically, the power analysis was conducted with respect to whole word accuracy, the primary outcome. Mplus [33] was used for power analysis with a sample size of 60 (30 per group). Mplus calculates power by simulating data given the design. In the simulation, the effect size is defined as change in the primary outcome between the low dose frequency group and the high dose frequency group divided by the square root of the model variance (a quantity similar to Cohen’s *d)*. At type one error of 5% (two tailed test) and a moderate treatment effect of 0.35, the power for estimating the treatment is 80%.

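### Similar gains after 24 sessions is one of three stated hypotheses, but the protocol powers only a test for a difference there and reads undetected differences as support for choosing the schedule freely

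*Protocol article*

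**What the plan says.** The Protocol article, Current study, makes three predictions. The first is similarity at equal cumulative dose: "We hypothesize that similar treatment and generalization gains will be detected for both the high and low dose frequency groups when cumulative dosage is constant", that is, after 24 sessions. The second is superiority at a fixed calendar time: "we predict that the high dose frequency group will demonstrate superior outcomes following 6 weeks of treatment". The third is better maintenance in the high dose frequency group. Potential significance repeats the first: "we posit that both groups will demonstrate comparable improvements following the full dose (24 h) of treatment".

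Targeted enrollment sizes one comparison only, on the primary outcome, "comparing the Lower Dose Frequency treatment group to the High Dose Frequency treatment group during the immediate-post testing period". It is a test for a difference: "At type one error of 5% (two tailed test) and a moderate treatment effect of 0.35, the power for estimating the treatment is 80" per cent. The effect is the between-group difference in change "divided by the square root of the model variance", and the calculation assumes 30 children per group.

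The Statistical analysis plan section and Data cleaning and preparation describe effect sizes and growth-curve comparisons between the groups. Neither section gives a margin, an equivalence test or an interval criterion for similarity.

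Potential significance then says how a null result would be read: "if treatment effects are shown but group differences are not detected, this will suggest that treatment schedule can be determined based upon available resources" and on family or clinician preference.

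**The concern.** A test for a difference cannot confirm similarity. If the first hypothesis is exactly true, the powered two-sided 5% test is non-significant 95% of the time. That outcome also occurs often when a real difference exists and the trial is too imprecise to show it. The two situations can be told apart only by asking which differences the confidence interval excludes, and the article sets no such criterion.

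What is at stake is the practice conclusion. As worded, the less precise the trial, the more easily it concludes that schedule can follow resources and preference. Services and families could act on that while a relevant disadvantage of either schedule remains inside the interval. The background section on Treatment intensity frames the question in the same two-way form: one schedule is superior, or the choice is free. It leaves no place for an inconclusive result.

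**Working it through.** **Inputs.** From Targeted enrollment: 30 per group, two-sided 5% level, standardized effect 0.35, power 80%. The documents give no similarity margin and no variance components. The margins below (0.20, 0.25, 0.35) are therefore assumptions, shown as a range.

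**1. The plan's own figure.** A plain two-sample comparison with SD 1 has SE = √(2/30) = 0.258. Its two-sided power at 0.35 is about 27%, not 80%. The protocol's figure comes from a latent growth curve simulation with repeated probes, so this does not show it to be wrong. The SE that 80% power implies is

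0.35 / (1.960 + 0.842) = 0.125.

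The variance ratio is (0.1249/0.2582)² = 0.234, so the model would have to remove about 77% of the simple variance. With five baseline and two post-treatment probe sets and an assumed exchangeable correlation of 0.6 to 0.7, power comes to 74–85%. The stated 80% is therefore plausible but cannot be reproduced from the stated inputs. The steps below take it at face value.

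**2. How often one contrast is non-significant.** P(non-significant) ≈ Φ(1.96 − d/0.1249).

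| True difference d | d/SE | P(non-significant) |
|---|---|---|
| 0.35 | 2.80 | 20% |
| 0.25 | 2.00 | 48% |
| 0.20 | 1.60 | 64% |

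**3. What a non-significant interval can contain.** The 95% half-width is 1.96 × 0.1249 = 0.245. An estimate is non-significant when its absolute value is below 0.245. The interval still reaches 0.35 when that value is above 0.35 − 0.245 = 0.105. So non-significant estimates between 0.105 and 0.245, in either direction, leave the protocol's own design effect unexcluded.

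**4. Worst-case bound.** With the unadjusted SE of 0.258, P(non-significant) at 0.35 is 73% and the 95% half-width is 1.96 × 0.258 = 0.51. The trial does not plan that analysis.

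**5. Power to show similarity.** The criterion is two one-sided tests at 5% each, equivalent to the 90% interval lying inside ±m. At zero true difference, power = 2Φ(m/SE − 1.645) − 1, set to 0 if negative. With SE 0.1249 the 90% half-width is 0.206.

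| Assumed margin m | m/SE − 1.645 | Power, 30 per group | n per group for 80% power |
|---|---|---|---|
| 0.35 | 1.157 | 75% | 33 |
| 0.25 | 0.356 | 28% | 65 |
| 0.20 | −0.044 | near nil | 101 |

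The last column is 2 × ((1.645 + 1.282)/m)² rounded up (140, 275 and 429), multiplied by 0.234 and rounded up. Under the unadjusted SE the 90% half-width is 1.645 × 0.258 = 0.425, wider than any of these margins, so power is nil.

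**The case against.** The strongest reply is that similarity is only one prediction among three. The article's summing-up of its hypotheses stresses faster gains and better maintenance with high dose frequency, and difference tests suit those claims. This stands. A reader might infer that similarity is the main hypothesis because it is stated first and sits at the powered time point, but the documents never call it that.

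A reader might also take the Discussion sentence as a decision rule triggered by the 24-session contrast alone. The text does not support that. The sentence is the alternative to the whole set of predictions, is not tied to one time point, requires that treatment effects are shown, and says only that the result would suggest something. If gains are similar after 24 sessions but differ elsewhere as predicted, it does not apply. The percentages in the working are therefore non-rejection rates for one contrast, not the probability that the trial reaches the practice conclusion.

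It is also tempting to lead with the 73% figure. That assumes one measurement per child and no adjustment, whereas the trial has repeated probes and a growth model. At the protocol's own precision, the 20% at 0.35 is the ordinary type II error of an 80%-powered trial.

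Finally, an unseen statistical analysis plan may contain a margin, and the article does plan to compare effect sizes between groups. So it cannot be said that no criterion exists anywhere. But the article itself fixes the hypothesis, the difference-only power basis and the reading of a null result. A margin set elsewhere would conflict with the Discussion sentence as it stands.

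**Conclusion.** The concern holds in this limited form. The protocol predicts similarity after 24 sessions, powers only a difference test at that point, gives no interval-based criterion for similarity, and bases a practice conclusion on differences not being detected.

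At the precision implied by the stated 80% power, the chance of missing a difference on a single contrast runs from 20% (true difference 0.35) to 64% (0.20). The power to show similarity properly runs from about 75% to near nil over assumed margins of 0.35 down to 0.20. These figures rest on the implied SE of about 0.125, a normal approximation and, for the similarity power, a true difference of zero.

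The value 0.35 should not be read as a ready-made margin. The protocol calls it a moderate effect, so using it would allow nearly moderate differences to be labelled similar. Randomization, the primary outcome and the superiority comparisons are unaffected. Severity: should-fix.

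**What to change.** Before any between-arm outcome comparison:

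1. State and justify a similarity margin for the contrast after 24 sessions, on the scale used for the effect size.
2. Claim similarity only if the 90% confidence interval for the high-minus-low difference (two one-sided tests) lies inside that margin.
3. Report the power for that criterion alongside the existing 80%.
4. Reword Potential significance so that a non-significant result whose interval reaches beyond the margin is reported as inconclusive and does not support choosing by preference.
5. Keep the difference tests for the 6-week and maintenance hypotheses.

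This costs wording, one more interval and a further power statement; it needs no extra visits or data. The real price is that the trial may have to report an inconclusive result where it would have claimed similarity. With a margin well below 0.35 that is likely at the planned 30 per group, and the sponsor should know it in advance.

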### Potential limitations

As noted above, assessments and treatment in the proposed study will be conducted by community speech-language pathologists. Although engaging community clinicians in this study will help to increase the application, external validity, and translation of this research, it may result in potential limitations as well. To start, DTTC is considered a dynamic and individualized treatment that relies on the clinician’s ability to monitor and cue the child to promote speech accuracy. The clinical experience of our community clinicians will vary which could introduce clinician effects. However, the randomization of participants to groups should help to minimize any effects of the clinician or clinical environment. In addition, to help address the varied expertise of the clinician partners working in this study, all clinicians will be required to undergo 20 h of training focused on assessment and treatment protocols and study procedures. Fidelity measures will also ensure that all clinicians, regardless of their prior experience, will adhere to the study protocols. Additional training and guidance will be given if needed. Clinicians will also meet in a group with the research team twice per month for ongoing training and problem-solving as needed. There is also the possibility that children may be challenged with the intensive treatment schedule and 60-min sessions where they are engaged in structured practice. As DTTC is focused on conscious practice of speech production, children may become frustrated and fatigued during sessions. As part of the clinical training and group meetings, strategies have been presented to support clinicians in their ability to maintain engagement, build trust and rapport, and practice at optimal challenge levels for each individual child. Group meetings will also offer clinicians the opportunity to review clinical cases and approaches for supporting children across the treatment phase.

Clinical research conducted in a lab often has the benefit of employing research assistants to help manage audio-visual recording for probes and treatment sessions, which helps to ensure high-quality recordings and to minimize data loss. By contrast, the community clinicians employed in this study will have to manage clinical care along with recordings and other logistics, which may result in occasional data loss if a video recording is not started appropriately or if there is a technical difficulty. To prevent missing data, all probes will also be audio recorded with a separate device as backup in case the video recording fails. Other safeguards will also be in place to ensure that clinicians provide assessments and treatment in a standardized way while also managing the many other requirements of research data collection. Examples of these safeguards include emails or text messages sent to clinicians prior to probe sessions as a reminder of tasks that need to be completed, daily session checklists indicating all activities to be completed during each session, and a study manual that provides detailed, operationalized protocols and procedures.

Difficulty with recruitment is also a potential challenge. While CAS is a relatively rare disorder occurring in only 1/1000 children [3], by including over 20 community clinicians across North America, we should be able to recruit the 60 participants required for the proposed study. We anticipate that some families may prefer to come 4 times per week while others may view that as too much of a burden and would prefer to come only twice a week. Given that this is an RCT, family preference will not be a factor in group assignment. To help support families who may be concerned about transportation and/or childcare of their other children while they are bringing a participant to treatment, a stipend of $40 will be provided for each session the child attends.

This study will compare two different treatment schedules and, consequently, it is imperative that children attend according to the prescribed schedule. While missing sessions due to illness such as COVID-19 cannot be avoided, it is possible to schedule study participation around other commitments such as vacations and holidays. To avoid preventable absences from treatment and follow-up sessions and ensure adherence to the study protocol, each clinician will work through the entirety of the study schedule with families prior to conducting baseline testing. Families will sign off in agreement to all dates from baseline through the 12-week follow-up before these activities begin.

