## Methods and design

The proposed work is a multisite Phase III parallel-group RCT that aims to investigate the outcomes of DTTC in children with CAS (ages 2;6 to 7;11) and determine whether dose frequency impacts response to treatment. Participants will be randomly assigned to receive DTTC treatment at a low dose frequency (2x/week over 12 weeks) or high dose frequency (4x/week over 6 weeks). Group assignment will be performed using concealed randomization. All assessments and treatment will be provided by community SLPs throughout North America. All of the clinicians working on this study will undergo a rigorous application process, as well as extensive training including numerous applied activities. They will receive ongoing feedback from the investigators, who are SLPs with expertise in CAS, throughout the study to ensure high adherence to experimental protocols and fidelity to the operationalized assessment and treatment approaches.

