#### Group allocation

For participants who meet inclusionary criteria following the eligibility assessment, group allocation will be specified by the study statistician using a computer-generated random number list. The group assignments will be put into sequentially numbered, opaque, sealed envelopes with the specified group number indicated inside the envelope. This will help to conceal the randomization sequence until group assignments are made. The study statistician will generate confidential treatment assignments for participants 1 through 30 and participants will receive their group assignment in the order in which they are enrolled in the treatment phase. After 30 participants are enrolled, we will conduct preliminary group comparisons of participant demographics to determine the extent that the groups are balanced. If there are statistically significant differences between groups on potentially confounding demographic variables such as age, language ability, or speech severity, we will attempt to rebalance the groups for the subsequent 30 participants who are enrolled. Speech severity will be established through combined analysis of scores from dynamic motor speech skill assessment (DEMSS) and single word articulation testing (*GFTA-3*). In cases where a participant withdraws prior to the completion of the study, the next participant to enroll will be assigned to the same treatment condition to be the substitute. Participants and clinicians will be told which group each participant is assigned to by the research team after the informed consent document has been signed and eligibility has been determined by the eligibility assessments.

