Growth curve modeling considers change over time as an underlying latent process. In analyzing this process, a trajectory of change over time is established for each individual in a sample, and therefore, characteristics of the trajectory (e.g., slope) may vary across individuals and are treated as latent variables. These latent variables describe parameters of change and may be treated as independent, dependent, control, or mediating variables and be compared across groups. Specifically, the growth curve model will allow us to (a) compare the treatment effect between Low Dose Frequency treatment and High Dose Frequency treatment groups during the treatment stage; (b) compare groups on maintenance effects during the post-treatment stage; (c) explain variations in change by incorporating various predictors. The growth curve model will also allow us to model flexible patterns of change in time such as quadratic and piecewise forms. Analyses will be conducted using Mplus software 5.0 [33].

Throughout our modeling process, we will carefully consider potential confounders that should be added to the model as covariates, such as severity of impairment, number of blocks practiced per session, age, and sex of the children. In the presence of attrition, an intention to treat analysis will be performed and compared with the analysis done on the “per protocol” population whenever possible. Baseline characteristics of the completed and withdrawn participants will be compared to prevent selection bias in the conclusions. In addition, internal validity (i.e., how well the randomization worked to create similar study groups) will be checked by comparing the groups on relevant measures using analyses of variance.

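### Families appear to sign off on their visit dates after learning the arm and before the first MACS probe, so refusals could differ by arm and leave no primary-outcome data.

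*Protocol article*

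**What the plan says.** Four parts of the protocol article bear on this point.

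- **Disclosure of the arm (Group allocation).** Participants and clinicians learn the assignment "after the informed consent document has been signed and eligibility has been determined by the eligibility assessments". A participant who withdraws is replaced by giving the next enrolee the same condition.
- **Sign-off (Potential limitations).** To prevent avoidable absences, "each clinician will work through the entirety of the study schedule with families prior to conducting baseline testing". Then: "Families will sign off in agreement to all dates from baseline through the 12-week follow-up before these activities begin".
- **Burden (Potential limitations).** Some families may prefer four visits a week, while "others may view that as too much of a burden and would prefer to come only twice a week". The article's answer is that "family preference will not be a factor in group assignment". A stipend of $40 per attended session is offered.
- **Analysis (Statistical analysis plan).** "In the presence of attrition, an intention to treat analysis will be performed", to be compared with a per-protocol analysis. Baseline characteristics of completers and withdrawals will also be compared.

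Ability to attend either schedule is not among the 12 inclusion criteria listed under Participants. The article does not say what happens to a family that will not sign.

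**The concern.** Keeping preference out of the assignment protects the assignment only. A family that learns its arm and is then asked to commit to that arm's dates can still act on its preference by not signing. If more families refuse in one arm than in the other, the children who go on to be probed no longer form the groups that were randomised.

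The timing makes this hard to repair. A refusal at sign-off would come before any MACS score exists, so an intention-to-treat analysis has no primary outcome for that child. If a refusal is handled as a withdrawal, the same-arm substitution rule would refill the place with a family able to attend.

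If families able to attend four times a week also tend to gain more, the bias favours high dose. That is the direction hypothesised for the 6-week comparison and for maintenance, and it would blur the similarity that is predicted after 24 sessions.

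**Working it through.** **Step 1: order of events.** No arithmetic applies here, so the sections are set side by side.

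1. Group allocation: consent, then the eligibility assessment, then the arm is disclosed.
2. Potential limitations: the whole schedule is worked through and all dates are signed before baseline testing.
3. Table 2: the dates depend on the arm. High dose has 24 sessions in weeks 1 to 6, the 4-week follow-up in week 10 and the 12-week follow-up in week 18. Low dose has 24 sessions in weeks 1 to 12, with the same follow-ups in weeks 16 and 24. A single list of all dates cannot be filled in without knowing the arm.
4. Baseline phase: the first MACS-scored probes are P1 to P3, in the two to three weeks before treatment.

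The implied order is consent, eligibility, disclosure, sign-off, P1 to P3, treatment. Putting disclosure before sign-off is an inference from item 3; no sentence states it.

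**Step 2: data held on a child lost at sign-off.** There would be no MACS score at P1 to P10. The eligibility battery would already have supplied ICS and FOCUS-34 (both secondary outcomes), as well as GFTA-3, DEMSS, language scores and age.

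**Step 3: size of the bias.** Let q_H and q_L be the proportions refusing in the high- and low-dose arms. Let D be the mean gain of families who stay minus that of families who refuse, in SD units and taken as equal in both arms. Losing a fraction q raises an arm's mean by q × D, so

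bias = (q_H − q_L) × D.

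None of these inputs is in the article. Assume q_L = 3% and D = 0.5 SD:

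| q_H (assumed) | Bias (SD) | Share of the 0.35 planning effect |
|---|---|---|
| 10% | (0.10 − 0.03) × 0.5 = 0.035 | 10% |
| 15% | (0.15 − 0.03) × 0.5 = 0.060 | 17% |
| 30% | (0.30 − 0.03) × 0.5 = 0.135 | 39% |

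With D = 0, or with equal refusal in both arms, the bias is zero. If refusal were higher in the low-dose arm, the sign would reverse.

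The last column treats 0.35 as SD units. Targeted enrollment describes it as a quantity similar to Cohen's d, so the shares are approximate.

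**Step 4: effect on the test.** The planned power is 80% at an effect of 0.35, with 30 per group and two-sided 5%. It comes from a growth-curve simulation whose variances are not given, so it can be neither reproduced nor refuted here. A plain two-group comparison with SD 1 gives 27.3%. Taking the stated 80% at face value, the implied standard error is 0.35 / (1.960 + 0.842) = 0.125. With D = 0.5 SD and a net difference in refusal (q_H − q_L) of 10, 20 or 30 percentage points:

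- 10 points: bias 0.05 SD, two-sided type I error 6.9%
- 20 points: bias 0.10 SD, two-sided type I error 12.6%
- 30 points: bias 0.15 SD, two-sided type I error 22.5%

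By contrast, losing 10%, 20% or 30% of the high-dose arm without replacement lowers power from 80% to 77.8%, 75.2% or 72.0%. The main issue is bias, not lost power.

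**The case against.** The sign-off is presented as a tool for adherence, to schedule around holidays and other commitments. The article does not say that a family who declines is excluded, or that dates cannot be renegotiated. Nor does it rule out agreement to both calendars before disclosure. The research team describes the study in more detail before consent, so families who could not manage four visits a week may decline then. Treatment may be given at home, and the stipend eases transport and childcare. A fuller protocol or study manual may contain a check that the article omits.

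Much of this stands, and it limits what can be claimed. Four stronger readings are tempting but unsupported:

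- **That the sign-off is a stated entry condition.** It is not listed as one, and the consequence of not signing is not given. Loss at this step is a risk, not a described event.
- **That only the high-dose arm would lose families.** Low-dose families commit to 12 treatment weeks and to follow-up through week 24, and may refuse that longer calendar. The article also expects some families to prefer four visits a week.
- **That refusers would have no outcome data at all.** This is true of MACS. It is not true of ICS and FOCUS-34, which are in the eligibility battery.
- **That the selection would work through a known route to better gains.** The article provides nothing to establish one.

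What the objection does not remove is the ordering. A general description before consent and a stipend do not secure agreement to either schedule before allocation. Comparing completers with withdrawals can describe a selective loss, and covariates can adjust for part of it, but neither supplies the missing MACS scores.

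**Conclusion.** The point holds as a risk created by the apparent order of disclosure and sign-off. Refusals could differ by arm, plausibly with more in the high-dose arm, and the children concerned would be missing from the primary analysis. Disclosure before sign-off is a strong inference from the arm-specific dates. Loss of non-signers, and their replacement within the same arm, are possibilities that the article leaves open.

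The size cannot be fixed from the article. The range of 0.035 to 0.135 SD rests wholly on assumed refusal rates and an assumed 0.5 SD difference in gain; its upper end needs 30% refusal in one arm. The only loss figure in the article is a 10% attrition allowance overall. The change is worth making because it is cheap and protects the randomised comparison, not because a large bias has been shown.

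**What to change.** Before the envelope is opened, have the caregiver and the treating clinician agree to both dated calendars, each running through its own 12-week follow-up. Make this agreement an inclusion criterion, and move the sign-off described under Potential limitations to this point. Do not randomise families who can accept only one calendar, and count them in the screening log. Report by arm any child who is randomised but does not start, since a family may still change its mind once the arm is known.

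If agreement to both schedules is already obtained before disclosure, it is enough to say so in the text.

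The cost is a change of wording and one extra calendar per family. Some families will be declined before randomisation. Recruitment would be somewhat slower, which matters because the article already names recruitment as a challenge. The results would apply to families able to accept either schedule. Neither treatment schedule changes.
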